## **7 ASSESSMENTS AND METHODS**

### **7.1 Baseline Data**

The baseline information and medical history will be recorded during Visit 1, i.e., as soon as possible after randomization.

#### **7.1.1 Demographic and Baseline Characteristics**

The demographic and baseline characteristics are sex, age, height, weight, and Body Mass Index (BMI).

#### **7.1.2 Medical History and Prior/Concomitant Medications**

The medical history will be obtained by interviewing the patient or from the medical records.

Prior and concomitant medications will be obtained.

### **7.2 Study Assessments**

#### **7.2.1 Surgical and Surgery-Related Data**

The following surgical data will be collected: details of procedure, CPB duration, CPB start and end times, cross-clamp duration, circulatory arrest duration, fluid intake and output, any medications administered, hemodynamic support (e.g., IABP), as well as any blood conservation methods used (e.g., hemoconcentration, retrograde prime, cell salvage).

In addition, extubation time, ICU length of stay, and hospital length of stay will be documented.

#### **7.2.2 Transfusion Data**

Details of all blood products and hemostatic agents released from the blood bank and transfused will be collected from the blood bank databases. These include allogeneic blood products (RBCs, pooled or apheresis platelets, and plasma) and albumin. Other hemostatic agents include: desmopressin, fibrinogen concentrates, rFVIIa, idarucizumab, and andexanet alpha.

#### **7.2.3 Bleeding Data**

The comparison of 'major' bleeding based on the validated e-CABG and universal definition of perioperative bleeding (UDPB) in cardiac surgery (1, 72) (Table 4) will be assessed. The UDPB is a multistage definition for perioperative bleeding based on easily measured clinical end points, including total blood loss from chest tubes within 12 hours, allogeneic blood products transfused, surgical re-exploration including cardiac tamponade, delayed sternal closure, and the need for salvage treatment.

Depending on these components, bleeding is graded as insignificant, mild, moderate, severe, or massive. (Table 4) (72).

**Table 4 Bleeding categories according to the UDPB in adult cardiac surgery (if different categories indicate mixed definitions of bleeding, the worst definition applies) (72)**

| Bleeding definition     | Postoperative chest tube blood loss within 12 h (mL) | RBC (units) | FP (units) | PLT (units) | Cryoprecipitate | PCCs | rFVIIa | Reexploration /tamponade |
|-------------------------|------------------------------------------------------|-------------|------------|-------------|-----------------|------|--------|--------------------------|
| Class 0 (insignificant) | <600                                                 | 0           | 0          | 0           | No              | No   | No     | No                       |
| Class 1 (mild)          | 601–800                                              | 1           | 0          | 0           | No              | No   | No     | No                       |
| Class 2 (moderate)      | 801–1000                                             | 2–4         | 2–4        | Yes         | Yes             | Yes  | No     | No                       |
| Class 3 (severe)        | 1001–2000                                            | 5–10        | 5–10       | N/A         | N/A             | N/A  | No     | Yes                      |
| Class 4 (massive)       | >2000                                                | >10         | >10        | N/A         | N/A             | N/A  | Yes    | N/A                      |

FP, frozen plasma; N/A, not applicable; PCC, prothrombin complex concentrate; PLT, platelets; rFVIIa, recombinant activated factor VII; UDPB, universal definition of perioperative bleeding.

To remove any potential bias from PCC and/or FP dosing, as their use is dictated by the randomization schedule, a modified version of the UDPB will also be applied, with the following components of the score omitted: transfusion of PCC, and transfusion of FP.

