| Pooled and apheresis platelets                                          |                    | X                                          | X                     |                   |
| Plasma                                                                  |                    | X                                          | X                     |                   |
| Fibrinogen concentrates                                                 |                    | X                                          | X                     |                   |
| Cryoprecipitate                                                         |                    | X                                          | X                     |                   |
| Other hemostatic products                                               |                    | X                                          | X                     |                   |
| Blood loss determination (e-CABG, UDPB and modified UDPB e ) |                    | X                                          | X                     |                   |
| Extubation time                                                         |                    | X                                          | (X)                   | (X)               |
| ICU length of stay                                                      |                    | X                                          | (X)                   | (X)               |
| Hospital length of stay                                                 |                    |                                            | X                     | (X)               |
| AEs and SAEs                                                            |                    | X                                          | X                     | X                 |
| Concomitant medications                                                 |                    | X                                          | X                     | X                 |

AE, adverse event; CPB, cardiopulmonary bypass; DC, discharge; ICU, intensive care unit; POD, postoperative day; SAE, serious adverse event; UDPB, universal definition of perioperative bleeding; e-CABG, European Coronary Artery Bypass Grafting SDM- Surrogate Decision Maker

\*For any activities not completed during this visit, additional visits will be undertaken to complete activities

a After the start of surgery.

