### 6.1.2 Visit 1: First post-randomization visit (0 to 24 hours after randomization)

For any specified activity that cannot be completed on this visit, additional visits will be made until all study data are obtained.

- Obtain consent from patient or surrogate
- Collect baseline data
  - Demographics
  - Medical history
  - Preoperative concomitant medications
- Collect surgical data
  - Intraoperative concomitant medications
  - CPB start and end times
  - Cross-clamp time
  - Circulatory arrest start and end times
  - Fluid in- and output monitoring
  - Inotropes and vasopressors
- Collect laboratory assessments where available as part of routine care
  - Chemistry (sodium, potassium, chloride, bicarbonate, pH)

- Hematology (complete blood count)
  - Coagulation profile before and after IMP administration
  - Safety labs (creatinine, liver function tests [ALT, ALP], bilirubin, troponin)
- Collect all transfusion and hemostatic agents (number and timing) for the 24 hour period after randomization
- Collect bleeding components using the e-CABG and UDPB criteria (1, 72) as well as a modified version of the UDPB not including PCC and FP requirements
- Collect extubation time
- Collect concomitant medications
- Collect AEs and SAEs

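### Protocol 7.2.3 counts delayed sternal closure as a UDPB component, but Table 4 has no column or class for it, so the bleeding grade, chiefly in the modified UDPB, can come out too low

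*Combined protocol and SAP*

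**What the plan says.** Protocol section 7.2.3 lists the end points that make up the UDPB: chest-tube loss within 12 hours, allogeneic products transfused, and then "surgical re-exploration including cardiac tamponade, delayed sternal closure, and the need for salvage treatment". It continues: "Depending on these components, bleeding is graded as insignificant, mild, moderate, severe, or massive", and refers to Table 4.

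Table 4 grades on chest-tube loss, RBC, FP, platelets and cryoprecipitate, followed by the columns "PCCs | rFVIIa | Reexploration /tamponade". Its title gives the rule for combining them: "if different categories indicate mixed definitions of bleeding, the worst definition applies". The modified UDPB is the same score "with the following components of the score omitted: transfusion of PCC, and transfusion of FP".

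On data collection, Visit 1 (section 6.1.2) says "Collect bleeding components using the e-CABG and UDPB criteria (1, 72) as well as a modified version of the UDPB". The flow chart (Table 1) has a general row, "Blood loss determination (e-CABG, UDPB and modified UDPB". Section 7.2.1 collects details of the procedure together with items such as "cross-clamp duration, circulatory arrest duration, fluid intake and output, any medications administered, hemodynamic support". None of these names sternal closure.

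In the SAP, section 4.6 endpoint S2 analyses the UDPB, its individual components and the modified version, without listing the components. Section 6.1 derives treatment response and the blood-product sums. It has no derivation for either form of the UDPB.

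**The concern.** The text and the table of one section define the same score differently. The text makes delayed sternal closure an item in its own right, separate from re-exploration, and says the grade depends on it. The table that produces the grade cannot use it. A site that follows the text may record the item, and a programmer who follows Table 4 then has no class to give it.

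Because S2 reports the components as well as the grade, the component list is a direct input to the analysis. The modified UDPB matters most. It was introduced so that products dictated by randomization do not drive the score, and it removes only PCC and FP, so by the protocol's own description delayed closure should stay in. The pilot is meant to inform the outcome for Phase 3, and a bleeding score that can be derived in two ways is a weak candidate.

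**Working it through.** There is no stated figure to reproduce. The check compares the text with the table and then applies the table's rule.

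**1. Components against columns**

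| Item in the 7.2.3 text | Place in Table 4 |
|---|---|
| Chest-tube loss, 12 h | Own column |
| Allogeneic products | RBC, FP, platelet and cryoprecipitate columns |
| Re-exploration, including tamponade | Own column (Class 3) |
| Salvage treatment | Not named; the rFVIIa column (Class 4) is the nearest match |
| Delayed sternal closure | No column, no class |

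PCC is the remaining column, which makes eight criteria. The header and all five class rows agree on eight, so a column lost when the file was read is unlikely, though it cannot be fully excluded.

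**2. When the omission lowers a grade**

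Let *d* be the class intended for delayed closure and *m* the patient's worst class on the other criteria. Under the worst-category rule:

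- grade with the item = max(*m*, *d*)
- grade from Table 4 as written = *m*
- shortfall = max(0, *d* − *m*)

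**3. Unmodified UDPB**

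The ITT population is limited to patients who received PCC or FP (SAP section 3.4). In Table 4 any PCC gives Class 2. One full plasma dose is 3 U or 4 U (protocol section 5.1.2), which falls in the 2–4 U band, also Class 2. Two full doses are 2 × 3 = 6 U or 2 × 4 = 8 U, in the 5–10 U band, Class 3. So *m* ≥ 2 after any PCC or one full plasma dose, and the shortfall is at most max(0, *d* − 2):

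- *d* ≤ 2: 0
- *d* = 3: at most 1 class
- *d* = 4: at most 2 classes

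**4. Modified UDPB**

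With PCC and FP removed, six criteria remain and *m* can be 0. The shortfall can then be as large as *d*, and it arises whenever *d* > *m*.

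**5. Size in the trial**

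This needs *d*, the class from which bleeding counts as 'major', the frequency of delayed closure, and *m* in those patients. The documents give none of these. The only scale available is that, with 50 evaluable patients per arm, each patient moved across a cut-off changes that arm's proportion by 1/50 = 2 percentage points. That converts one patient into points; it does not estimate how many patients there are.

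**6. Boundaries in Table 4**

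- Chest-tube loss: Class 0 is below 600 mL and Class 1 starts at 601 mL, so exactly 600 mL has no class.
- FP: 0 U in Classes 0 and 1, then 2–4 U in Class 2, so exactly 1 U has no class. This cannot matter in the modified score, which omits FP, nor for a patient given PCC, who is already Class 2. It leaves a patient in the FP arm who received 1 U in total.

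**The case against.** The strongest reply is that the mismatch may change very little. In the unmodified score the Class 2 floor absorbs the omission unless delayed closure carries Class 3 or 4. The modified score keeps six criteria, and a patient with serious bleeding may reach a high class through RBC, rFVIIa or re-exploration. The endpoint is exploratory in a descriptive pilot, and no primary or safety endpoint uses Table 4. The same table applies to both arms. All of this stands, and it limits the importance of the point.

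Collection is also better covered than it first appears. Visit 1 calls for the UDPB components by reference to the criteria, section 7.2.3 names delayed closure among them, and section 7.2.1 takes details of the procedure. A reader might infer that the item is not collected at all. The documents do not support that: they show only that no list names it, and the eCRF is not part of them.

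The boundary gaps are close to harmless. The 600 mL gap lies between the two lowest classes, and the other criteria still return a class. Table 4 is presented as a published instrument, so its cut-points should be checked against the source before anyone edits them.

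The contradiction itself is not answered. No other section supplies a class for delayed closure, and the SAP gives no derivation that would settle which definition applies.

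**Conclusion.** The plan is wrong as written on this point, for an exploratory endpoint. Section 7.2.3 makes the grade depend on an item that its grading table cannot score. Applying Table 4 can under-grade a patient whose chest was left open, mainly in the modified UDPB.

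A reader might go further and conclude that all such patients are under-graded. That does not follow: a grade falls only when the item's class exceeds the patient's worst other criterion, and the documents do not state the item's class. Nor do they support a figure for patients misgraded or for a shift in the S2 rate, since any frequency of delayed closure or event rate would be assumed. Nothing in the documents points to a difference between arms.

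The conclusion rests on Table 4 having been read completely, and on the text's list being meant as the list of grading components, which is what section 7.2.3 says.

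**What to change.** 1. Reconcile the text of section 7.2.3 with Table 4. Add a delayed-sternal-closure column with the class given in the cited definition (reference 72), and state that the modified UDPB keeps it.
2. Name delayed sternal closure as a yes/no item in section 7.2.1 and at Visit 1. For patients already enrolled, look for it in the procedure details already collected.
3. Put the derivations of the UDPB and the modified UDPB in SAP section 6.1 before any unblinded analysis, with the component list, the class for each component, and the class from which bleeding counts as 'major'.
4. As a minor tidy-up, check the Table 4 boundaries against reference 72 so that exactly 600 mL and exactly 1 U of FP each return a class.

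The cost is one table edit, one yes/no data item, and one added derivation covering both forms of the score. Sample size, randomization and the primary endpoints are untouched.

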### 7.3 Laboratory Assessments

#### 7.3.1 Test Parameters and Laboratories (Only if performed as part of standard of care)

Table 5 summarizes all test parameters and the laboratories responsible for analysis.

**Table 5 Test parameters and laboratories**

| Test                                                        | Material needed | Responsible laboratory |
|-------------------------------------------------------------|-----------------|------------------------|
| Coagulation profile                                  |                 |                        |
| (PT, PTT, INR, fibrinogen activity via Clauss assay)        | Citrated blood  | Local                  |
| ROTEM EXTEM CT                                              | Citrated blood  | Local                  |
| ROTEM EXTEM MCF                                             | Citrated blood  | Local                  |
| PlateletWorks                                        | Fresh blood     | Local                  |
| Hematology – standard panel as per local lab         | Citrated blood  | Local                  |
| Clinical chemistry – standard panel as per local lab | Serum           | Local                  |
| Safety labs                                          |                 |                        |
| Troponin                                                    | Serum           | Local                  |
| ALT/ALP                                                     | Serum           | Local                  |
| Bilirubin                                                   | Serum           | Local                  |
| Creatinine                                                  | Serum           | Local                  |

ALT, alanine aminotransferase; ALP, alkaline phosphatase; CT, clotting time; MCF, maximum clot firmness; PT, prothrombin time; PTT, partial thromboplastin time; ROTEM, thromboelastometry

### 7.3.2 Blood Sampling

All blood sampling will be performed as per standard practice at the local institution.

The *actual* time of blood sampling will be recorded in the CRF. If the draw time is not recorded for samples processed in the laboratory, the draw time will be estimated based on the received time in the laboratory minus 10 minutes. For ROTEM and PlateletWorks, if the exact draw time is not recorded, the time for start of testing will be used for draw time.

### 7.3.3 Citrated and Fresh Blood

Citrated and fresh blood as required by the local laboratory will be collected and processed in accordance with local requirements.

### 7.3.4 Serum

Serum will be obtained for the determination of clinical chemistry and safety labs (ALT, ALP, creatinine, bilirubin, troponin), where a serum blood sample has been collected.

### 7.3.5 Recording of Clinically Significant Abnormal Laboratory Values as AEs/ADRs

Other than abnormal laboratory values due to the underlying condition, the Investigator must assess the clinical significance of abnormal laboratory values outside the specified normal range (see **Section 7.4**). Any clinically significant abnormalities will be documented. All specified clinically significant abnormalities will be documented as AEs/SAEs and investigated.

Additional tests and other evaluations required to establish the significance or etiology of specified abnormalities or to monitor the course of an AE will be obtained if clinically indicated. Follow-up will persist until resolution or up to the Study Completion Visit, whichever occurs first.

## 7.4 Safety Assessments

### 7.4.1 Assessments for Safety Endpoints

The following drug safety information will be collected:

- AEs and SAEs temporally associated with the administration of IMP (for definitions and reporting requirements, see **Sections 7.4.2, 7.4.3, and 7.4.4**).
- Pregnancies, drug overdose, interaction, medication error, and lack of efficacy (see **Section 7.4.5**).

#### 7.4.2 Adverse Events (AEs)

##### Definitions

**Adverse event (AE):** An AE is any untoward medical occurrence in a study patient receiving an IMP and which does not necessarily have a causal relationship with this treatment. An AE can therefore be any unfavorable and unintended sign (including an abnormal laboratory finding), symptom, or disease temporally associated with the use of an IMP, whether or not related to the IMP.

**Adverse drug reaction (ADR):** An ADR is any noxious and unintended response to an IMP related to any dose. The phrase ‘response to an IMP’ means that a causal relationship between the IMP and an AE carries at least a reasonable possibility, i.e., the relationship cannot be ruled out.

**Other significant AEs:** Any marked laboratory abnormalities or any AEs that lead to an intervention, including withdrawal of drug treatment, dose reduction, or significant additional concomitant therapy.

**Withdrawal due to AE/ADR:** AE/ADR leading to discontinuation of treatment with IMP. Any such events will be followed up by the Investigator until the event is resolved or until the medical condition of the patient is stable. All follow-up information collected will be made available to the Principal Investigator (Sponsor).

##### Collection of AEs

The condition of the patient will be monitored throughout the study. At each visit, whether scheduled or unscheduled, AEs will be elicited using a standard non-leading question such as “How have you been since the last visit/during the previous study period?” In addition, the research assistant will check the patient records for any documented event.

Any AE or ADR which occurs during the study will be noted in detail on the appropriate pages of the CRF. If the patient reports several signs or symptoms representing a single syndrome or diagnosis, the diagnosis should be recorded in the CRF. The Investigator will grade the severity of all AEs or ADRs (mild, moderate, or severe), the seriousness (non-serious or serious), and the likelihood that they were related to the IMP (causality). The Sponsor will be responsible for assessing the expectedness of each ADR (expected or unexpected).

Diseases, signs and symptoms, and/or laboratory abnormalities already present before the first administration of IMP will not be considered AEs unless an exacerbation in intensity or frequency (worsening) occurs.

The Investigator will provide detailed information about any abnormalities and about the nature of and reasons for any action taken as well as any other observations or comments that may be useful for the interpretation and understanding of an AE or ADR.

##### Severity of AEs

The intensity/severity of AEs will be graded as follows:

**Mild:** an AE, usually transient, which causes discomfort but does not interfere with the patient’s routine activities

**Moderate:** an AE which is sufficiently discomforting to interfere with the patient’s routine activities

**Severe:** an AE which is incapacitating and prevents the pursuit of the patient’s routine activities

The grading of an AE is up to the medical judgment of the Investigator and will be decided on a case-by-case basis.

### **Causality of AEs**

All AEs will be assessed by a blinded Investigator as to whether they can be explained by the patient's underlying condition or surgical course. If they are not explainable, then the Investigator will make a determination of the relationship of the AE with the IMP as follows:

**Probable:** reports including good reasons and sufficient documentation to assume a causal relationship, in the sense of plausible, conceivable, likely, but not necessarily highly probable. A reaction that follows a reasonable temporal sequence from administration of the IMP; or that follows a known or expected response pattern to the suspected medicine; or that is confirmed by stopping or reducing the dosage of the medicine and that could not reasonably be explained by known characteristics of the patient's clinical state.

**Possible:** reports containing sufficient information to accept the possibility of a causal relationship, in the sense of not impossible and not unlikely, although the connection is uncertain or doubtful, for example because of missing data or insufficient evidence. A reaction that follows a reasonable temporal sequence from administration of the IMP; that follows a known or expected response pattern to the suspected medicine; but that could readily have been produced by a number of other factors.

**Unlikely:** reports not following a reasonable temporal sequence from IMP administration. An event which may have been produced by the patient's clinical state or by environmental factors or other therapies administered.

**Not related (unrelated):** events for which sufficient information exists to conclude that the etiology is unrelated to the IMP.

**Unclassified:** reports which for one reason or another are not yet assessable, e.g., because of outstanding information (can only be a temporary assessment).

